# DIPS (Dystonia Image-based Programming of Stimulation: a prospective, randomized, double-blind crossover trial)

**DOI:** 10.1186/s42466-021-00165-6

**Published:** 2021-12-20

**Keywords:** Deep brain stimulation, Dystonia, Imaging-guided DBS programming

## Abstract

**Introduction:**

Deep brain stimulation of the internal globus pallidus is an effective treatment for dystonia. However, there is a large variability in clinical outcome with up to 25% non-responders even in highly selected primary dystonia patients. In a large cohort of patients we recently demonstrated that the variable clinical outcomes of pallidal DBS for dystonia may result to a large degree by the exact location and stimulation volume within the pallidal region. Here we test a novel approach of programing based on these insights: we first defined probabilistic maps of anti-dystonic effects by aggregating individual electrode locations and volumes of tissue activated of > 80 patients collected in a multicentre effort. We subsequently modified the algorithms to be able to test all possible stimulation settings of de novo patients in silico based on the expected clinical outcome and thus potentially predict the best possible stimulation parameters for the individual patients.

**Methods:**

Within the framework of a BMBF-funded study, this concept of a computer-based prediction of optimal stimulation parameters for patients with dystonia will be tested in a randomized, controlled crossover study. The main parameter for clinical efficacy and primary endpoint is based on the blinded physician rating of dystonia severity reflected by Clinical Dystonia Rating Scales for both interventions (best clinical settings and model predicted settings) after 4 weeks of continuous stimulation. The primary endpoint is defined as “successful treatment with model predicted settings” (yes or no). The value is “yes” if the motor symptoms with model predicted settings are equal or better (tolerance 5% of absolute difference in percentages) to clinical settings. Secondary endpoints will include measures of quality of life, calculated energy consumption of the neurostimulation system and physician time for programming.

**Perspective:**

We envision, that computer-guided deep brain stimulation programming in silico might provide optimal stimulation settings for patients with dystonia without the burden of months of programming sessions. The study protocol is designed to evaluate which programming method is more effective in controlling motor symptom severity and improving quality of life in dystonia (best clinical settings and model predicted settings).

*Trial registration* Registered with ClinicalTrials.gov on Oct 27, 2021 (NCT05097001).

## Introduction

Dystonia is a central nervous system disease associated with sustained or intermittent muscle contractions causing abnormal, often repetitive, movements, postures, or both [1]. Activities of daily living, social participation and quality of life can be markedly impaired in dystonia due to pain, reduced overall mobility and stigmatization [2, 3].

Deep brain stimulation (DBS) is a surgical therapy for a variety of neurological and psychiatric disorders that uses continuous electrical stimulation of deep brain nuclei to alter neural activity. There is class I evidence for the safety and efficacy of DBS applied to the internal globus pallidus (GPi) to suppress motor symptoms in dystonia [4, 5] with an average improvement of dystonia severity of 50 to 60% in most clinical studies [5– 8]. However, there is a large variability in clinical outcome with up to 25% non-responders (< 25% motor score improvement) even in highly selected primary dystonia patients. In a large cohort of patients collected from several European centers we recently demonstrated that the variable clinical outcomes of pallidal DBS for dystonia may result to a relevant degree by the exact location and stimulation volume within the pallidal region [9].

These results and the underlying cohort of > 80 patients were subsequently used to derive probabilistic maps of anti-dystonic effects by aggregating individual electrode locations and volumes of tissue activated (VTA). These maps and novel computer algorithms showed robustness between the predicted and observed clinical improvement with an R^2^ of 0.53 (*p* < 0.01) in a leave-one-out-cross-validation. On average, individual predictions differed from observed improvements in dystonia by only 16.9 ± 11.6%. Interestingly, the computer algorithms predicted a potential improvement for the cohort and a reduction in non-responders if patients were switched to the optimal stimulation settings determined by the algorithms (mean improvement: 16.9 ± 11.6% and 25% to < 5% non-responders) [9].

We subsequently modified the algorithms to test all possible stimulation settings of de novo patients in silico based on the expected clinical outcome and thus potentially predict the best possible stimulation parameters for the individual patients. Within the framework of a BMBF-funded study, this concept of a computer-based prediction of optimal stimulation parameters for patients with dystonia will be tested in a randomized, controlled crossover study.

## Methods

### Aim of the trial

Deep brain stimulation for dystonia is in principle highly effective, but clinical application lacks standardization and the therapy is largely skill and experience based, which results in variable patient outcomes, even in experienced centers. Prolonged latencies between changes in program settings and observed symptom changes (sometimes weeks or months) hinder optimization of stimulation settings based on clinical response evaluation, which is the gold-standard for parameter titration. The parameter space of DBS is confusingly large and the high numbers of variables and resulting stimulation options (> 1.000.000 options with modern DBS systems) prevents an exhaustive clinical search for the best possible settings. We envision, that this search could be reliably performed by our digital expert system, which would provide one or a few programming suggestions, which could then be further refined in clinical practice. Such an approach would be advantageous to patients and physicians, by reducing the programming burden, providing faster and more efficient symptom control for patients and reduced programming g time for neurologists.

### Study description and study design

This study will be conducted as a double-blind, randomized, cross-over trial. The overarching study flow is illustrated by Fig. 1. The study includes five phases: baseline visit, programming visit, randomization, motor visit I, and motor visit II.

**Fig. 1 Fig1:**
[figure not shown]
provides an overview of the course of study. Patients first undergo baseline visit and programming visit, then are randomized and blinded to two arms and receive either the computer-generated or the clinically generated program for 4 weeks. In the first motor visit, the patients are examined and then—still blinded—receive the other program for four weeks. Subsequently, in the second motor visit, the program is evaluated and the patients end the study with the choice of the better program

*At baseline visit*, standardized recordings of medical history and motor examination are performed. In addition to the neurological examination, the motor examination includes the video recording of the internationally used dystonia motor scores Toronto Western Spasmodic Torticollis Rating Scale (TWSTRS) and Burke–Fahn–Marsden Dystonia Rating Scale (BFMDRS). Health-related quality of life is assessed using SF-36 and CDQ24. To determine the immediate stimulator effect, the stimulator is switched off and the patients are examined in this Stim OFF condition (TWSTRS and BFMDRS) after 60 min. For a graphical representation of the visits and the respective examinations, please see Fig. 2.

**Fig. 2 Fig2:**
[figure not shown]
gives an overview of the examinations per visit. The visits are represented as a row below each other, the respective examinations as marked columns on the right-hand side

During *programming visit*, a DBS expert performs comprehensive reprogramming according to clinical best practices. This represents the usual procedure for initial setting of the stimulator after surgery. This process is described in detail in the section Clinical programming below.

According to *randomization* the unblinded programmer will activate one of the two programs (“*computer” or* “*clinical”*). Adequate measures to keep the patient blinded to the respective settings will be taken (ramp settings > 8 s and patient programmer display reduced to minimal settings). Patients will stay under physician supervision for around 30 min to check for any acute side effects.

*Motor visit 1* is scheduled 4 (± 1) weeks after randomization as the first follow-up. Again, standardized video recordings of the motor examination (TWSTRS/BFMDRS) and patient questionnaires (SF-36, CDQ24) will be taken to evaluate symptom severity and disease-related quality of life. The unblinded DBS programmer will then swap the programs (“*computer” to* “*clinical or* “*clinical” to* “*computer”*). Again, patients will stay under physician supervision for around 30 min to check for any acute side effects and will then be released into the second chronic phase. A telephone safety call 1 week after each change of stimulation parameters was implemented to allow for early response to any problems or suboptimal motor control.

*Motor visit 2* is scheduled 8 (± 1) weeks after randomization as the second follow-up. A third time, standardized video recordings (TWSTRS/BFMDRS) and patient questionnaires (SF-36, CGI) will be taken to evaluate symptom severity and patient’s program preference will be evaluated. The study concludes and the patients can decide which program will be activated for chronic use.

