### Outcome measures

The primary efficacy endpoint is based on the blinded physician rating of dystonia severity reflected by Clinical Dystonia Rating Scales (BFMDRS or TWSTRS). The raters will be internationally recognized leading experts in the field of movement disorders that are not part of the study team or otherwise related to our center. For both interventions (best clinical settings and model predicted settings) we will calculate the symptom severity score after 4 weeks of continuous stimulation, expressed in percent of the pre-operative score. The primary endpoint is defined as “successful treatment with model predicted settings” (yes or no). The value is “yes” if the motor symptoms with model predicted settings are equal or better (tolerance 5% of absolute difference in percentages) to clinical settings.

Secondary endpoints will include measures of quality of life (SF-36 and CDQ24 questionnaire), calculated energy consumption of the neurostimulation system and physician time for programming. The study aims at estimating the success rate and explorative characterization of treatment failures in preparation for a confirmatory multicentre clinical trial.

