#### Statistical analysis

Primary analysis of the primary endpoint: The exact two-sided 95% CI for the success rate will be computed from all patients with defined primary endpoint. In case the study will be stopped with n < 40, confidence limits will also be presented for the virtual scenarios with n = 40 and either success or non-success in all k “remaining” patients where n–k is the actual number of evaluable patients. The purpose of the primary analysis is to obtain advice for the hypothesis of a subsequent larger trial, as described in the sample size section.

For the clinical plausibility, we will examine if there might be differences in quality of life under the two stimulation modalities, and if these differences might be correlated with the measured functional data.

Note on the cross-over design: All analyses will be carried out just with methods for usual paired data. The effects of DBS are largely washed out after 48 h [12, 13] and our measurements will be obtained 4 weeks after a programming change. Therefore, carry over effects should be negligible. However, to rule out any wrong assumptions for the future trial, this study is being planned as a cross-over design, and the possibility of carry-over will be assessed for all endpoints under consideration.

The study database will be validated by the Clinical Trial Center Würzburg (CTCW). Web-based data entry during the study will ensure continuous data transfer to the CTCW. Central data checks and query management will ensure timely delivery and correctness of data. The data will be publically available after publication. ln accordance with the rules of good scientific practice and legal requirements, we will archive our data for at least 10 years.

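### Motor visit 2 is timed from randomisation instead of from the program swap, so the windows allow 2 to 6 weeks on the second program against 3 to 5 on the first (minor, one-line fix)

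*Protocol article*

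**What the plan says.** In the protocol article, the visit descriptions under Study description and study design (after the Fig. 2 legend) fix both motor visits from the same starting point:

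- Motor visit 1 is at 4 (± 1) "weeks after randomization as the first follow-up".
- At that visit, once the assessments are done, "The unblinded DBS programmer will then swap the programs".
- Motor visit 2 is at 8 (± 1) "weeks after randomization as the second follow-up".
- The safety contact has a different anchor: "A telephone safety call 1 week after each change of stimulation parameters".

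Three other places give the intended exposure as 4 weeks per program:

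- The Fig. 1 legend gives 4 weeks for the first program and then says that patients "receive the other program for four weeks".
- Outcome measures, on the primary endpoint for both interventions: "we will calculate the symptom severity score after 4 weeks of continuous stimulation".
- Statistical analysis, in the carry-over argument: "our measurements will be obtained 4 weeks after a programming change".

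The article gives no window counted from the swap and no minimum length for the second period.

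**The concern.** The primary endpoint compares the two programs within each patient, with a tolerance of 5 percentage points. The relevant clock is therefore time since the settings were changed, and it should run about equally long for both programs. The first program starts at randomisation, so anchoring Motor visit 1 there is right. The second starts at the swap, yet Motor visit 2 is still counted from randomisation. A late Motor visit 1 thus lengthens the first period and, for a given date of Motor visit 2, shortens the second by the same amount.

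Whether this matters depends on how fast a change of settings takes effect, and the article points both ways. Aim of the trial says that response can trail a change by weeks or even months. Statistical analysis says: "The effects of DBS are largely washed out after 48 h". If settling is slow, a patient rated 2 weeks after the swap, following 5 weeks on the other program, is not compared on equal terms. If it is fast, the difference in exposure has no practical effect.

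**Working it through.** **Inputs.** Visit windows from Study description and study design: Motor visit 1 in weeks 3 to 5, Motor visit 2 in weeks 7 to 9. Tolerance of 5 points from Outcome measures. n = 40 from Power calculation/sample size.

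**The plan's own figures.** The target dates give 4 weeks and 8 − 4 = 4 weeks, as stated. The exact two-sided 95% intervals at n = 40 are 50.9–81.4% for 27 successes, 48.3–79.4% for 26, 20.6–51.7% for 14 and 18.6–49.1% for 13. The stated cut-offs reproduce and do not depend on visit timing.

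**Permitted exposure (no assumption needed).**

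- First program: 3 to 5 weeks.
- Second program: shortest 7 − 5 = 2 weeks, longest 9 − 3 = 6 weeks.
- Largest within-patient difference: 5 − 2 = 3 weeks, or 6 − 3 = 3 weeks.
- With Motor visit 2 at 4 (± 1) weeks after the swap: second program 3 to 5 weeks, largest difference 5 − 3 = 2 weeks.

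**Typical exposure (assumption: visit dates vary independently within their windows, either uniformly or in a triangular distribution peaked at the target).** Let a and b be the deviations of visits 1 and 2 from their due dates, each between −1 and 1 week. As written, the second period is 4 + b − a and the gap (second minus first) is b − 2a. With the fix these become 4 + b and b − a.

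For uniform dates each deviation has variance 1/3. The SD of the second period goes from √(2/3) = 0.82 to √(1/3) = 0.58 weeks, and the SD of the gap from √(5/3) = 1.29 to √(2/3) = 0.82 weeks.

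| | Uniform: now → fix | Triangular: now → fix |
|---|---|---|
| SD of second period (weeks) | 0.82 → 0.58 | 0.58 → 0.41 |
| SD of gap (weeks) | 1.29 → 0.82 | 0.91 → 0.58 |
| Second period outside 3–5 weeks | 25% → 0 | 8% → 0 |
| Gap over 1 week | 50% → 25% | 29% → 8% |
| Gap over 2 weeks | 12.5% → 0 | 2.1% → 0 |

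**Effect on the endpoint (further assumptions: exponential response with time constant τ of 1, 2 or 4 weeks; first period settled; true differences between programs normal with mean 0 and SD 10 to 20 points).** After t weeks on the second program a true difference D is seen as D × (1 − exp(−t/τ)). A 5-point tolerance on the observed scale is then a tolerance of 5/(1 − exp(−t/τ)) on the true scale. Averaged over uniform visit dates:

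| τ (weeks) | Exactly 4 weeks | As written | With fix | Change due to fix |
|---|---|---|---|---|
| 1 | 5.09 | 5.13 | 5.11 | 0.02 |
| 2 | 5.78 | 5.89 | 5.83 | 0.06 |
| 4 | 7.91 | 8.14 | 8.02 | 0.12 |

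Triangular dates give about half these changes (0.01, 0.03 and 0.06 points).

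Expected successes are 40 × E[Φ(tolerance/SD)]. The largest change occurs with uniform dates, τ = 4 and SD 10: 31.63 as written against 31.52 with the fix, a change of 0.11. The smallest occurs with triangular dates, τ = 1 and SD 20, at 0.01. Dropping the assumption that the first period has settled gives the same range, 0.01 to 0.11 of 40.

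**The case against.** The strongest reply is that nothing measurable follows. About a tenth of one success in 40 has almost no bearing on a choice among success rates of 20%, 50% and 80%. Order is randomised, so neither program gains from the wider second window. This is correct, and it is why the point is graded minor.

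Second, the text can be followed consistently. For any Motor visit 1 in weeks 3 to 5, a Motor visit 2 exactly four weeks later falls in weeks 7 to 9. A site that books this way satisfies every statement and never produces a short or long period. That also stands. However, the statements of 4 weeks give a nominal duration, which does not override an explicit window. A site that books from the written schedule may still assess a patient 2 weeks after the swap.

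Third, the extremes are rare. With independent dates, a second period under 2.5 weeks has probability 3.1% (uniform) or 0.3% (triangular), and under 3 weeks 12.5% or 4.2%. Independence is itself an assumption.

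Fourth, the change does not equalise exposure: a gap of up to 2 weeks remains. Nor does it deal with slow settling. At τ = 4 weeks, 8.02 − 5 = 3.02 of the 8.14 − 5 = 3.14 points of excess tolerance, about 96%, remain afterwards, because they come almost entirely from the 4-week period length. Slow response is therefore mainly an argument about period length and only weakly one about the anchor.

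Finally, a safety call need not share its anchor with an efficacy visit, and a minimum-exposure rule may sit in the full protocol. Both are fair. The point rests on the window as written, not on something left out.

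**Conclusion.** The point holds as a minor inconsistency. The written windows permit 2 to 6 weeks on the second program against 3 to 5 on the first, while the article defines exposure as 4 weeks on each. These ranges follow directly from the printed windows. How often they would matter rests on an assumed spread of visit dates, and the effect on the endpoint on an assumed settling curve and spread of true differences. Across the ranges examined, the anchor changes the expected success count by no more than about 0.11 of 40. If effects settle within days, it changes nothing of practical note. No bias towards either program and no effect on the sample size or cut-offs was found. The case for acting is that the imbalance is avoidable at almost no cost.

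**What to change.** Schedule Motor visit 2 at 4 (± 1) weeks after the program swap at Motor visit 1. Both programs then have the same 3 to 5 week window, in line with the Fig. 1 legend, Outcome measures and Statistical analysis.

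The cost is one line in the visit schedule. Motor visit 2 would fall between weeks 6 and 10 from randomisation, so the last visit may come one week later than now. No extra visit, patient or change of analysis is needed.

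### CDQ24 is a secondary endpoint for paired analysis, but the visit text omits it at Motor visit 2, so as written no patient has a CDQ24 value under both programs

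*Protocol article*

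**What the plan says.** All references are to the Methods of the protocol article.

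- **Outcome measures** names the instruments: "Secondary endpoints will include measures of quality of life (SF-36 and CDQ24 questionnaire".
- **Study description and study design, baseline visit:** "Health-related quality of life is assessed using SF-36 and CDQ24".
- **Same section, Motor visit 1** (4 ± 1 weeks after randomization): "patient questionnaires (SF-36, CDQ24) will be taken to evaluate symptom severity and disease-related quality of life". At this visit, "The unblinded DBS programmer will then swap the programs".
- **Same section, Motor visit 2** (8 ± 1 weeks): "patient questionnaires (SF-36, CGI) will be taken to evaluate symptom severity". Program preference is also recorded. CDQ24 is not mentioned.
- **Statistical analysis**, on quality of life: "we will examine if there might be differences in quality of life under the two stimulation modalities", and whether such differences correlate with the functional data. On method: "All analyses will be carried out just with methods for usual paired data". On the crossover: "the possibility of carry-over will be assessed for all endpoints under consideration".

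CGI appears only at Motor visit 2. It is not among the endpoints in Outcome measures and is not in the abbreviation list.

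**The concern.** In a two-period crossover, a patient contributes to a paired comparison only if the outcome is measured at the end of both periods. The text does this for the motor scales and SF-36, but not for CDQ24. The endpoint and analysis sections therefore promise something that the visit text does not supply.

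At stake is the disease-specific one of the two quality-of-life instruments. The abstract's Perspective gives quality of life in dystonia as one of the two things on which the programming methods are to be compared. A CDQ24 not completed at the final visit cannot be recovered later, and the analysis section plans no between-patient fallback.

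**Working it through.** **1. Instruments by visit, from the text**

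| Visit | Settings in use | SF-36 | CDQ24 | CGI |
|---|---|---|---|---|
| Baseline | earlier chronic settings | yes | yes | no |
| Motor visit 1 | first-period program | yes | yes | no |
| Motor visit 2 | second-period program | yes | not listed | yes |

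SF-36 has one value per program and patient. CDQ24 has a value under the first-period program only, so 0 of 40 patients have a CDQ24 pair. Baseline cannot supply the missing value: it reflects the settings that had to be stable for at least 3 months before entry, and the clinical program under test comes from a comprehensive reprogramming done afterwards.

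**2. What this does to the planned analyses**

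- The paired CDQ24 difference between programs needs both periods, so it cannot be computed.
- Its correlation with the within-patient motor difference cannot be computed either.
- Carry-over assessment for CDQ24 needs data after the swap, and there are none.
- For SF-36 all three remain possible.

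**3. The plan's own figure**

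The plan gives no precision or power figure for CDQ24. The sample size of 40 evaluable participants is set by the primary endpoint. Exact two-sided 95% intervals at n = 40 reproduce the stated cut-offs:

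- 13 successes: 18.6% to 49.1% (contains only 20%)
- 14 successes: 20.6% to 51.7% (only 50%)
- 26 successes: 48.3% to 79.4% (only 50%)
- 27 successes: 50.9% to 81.4% (only 80%)

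That part is sound, and the CDQ24 gap does not touch it.

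**4. What is left for CDQ24, and what is lost**

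From the plan: n = 40. Assumed, because the article does not give them: a 20 v 20 split by sequence, equal SD under both programs, 80% power, two-sided 5%, and a correlation ρ of 0.5, 0.6 or 0.8, used both for baseline with Motor visit 1 and between the two periods.

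- Between patients at Motor visit 1, unadjusted (two-sample t-test, 20 + 20): detectable difference 0.909 SD.
- The same with baseline CDQ24 as covariate: 0.909 × √(1 − ρ²), ignoring the one degree of freedom spent on the covariate.
- Paired with 40 patients: the paired t-test detects 0.454 SD of the differences, which is 0.454 × √(2(1 − ρ)) in SD of the score.
- Variance ratio, unadjusted v paired: (2/20) / (2(1 − ρ)/40) = 2/(1 − ρ).
- Variance ratio, baseline-adjusted v paired: 2(1 − ρ²)/(1 − ρ) = 2(1 + ρ).

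| ρ | Unadjusted (SD) | Baseline-adjusted (SD) | 40 pairs (SD) | Variance ratio, unadjusted | Variance ratio, adjusted |
|---|---|---|---|---|---|
| 0.5 | 0.91 | 0.79 | 0.45 | 4.0 | 3.0 |
| 0.6 | 0.91 | 0.73 | 0.41 | 5.0 | 3.2 |
| 0.8 | 0.91 | 0.55 | 0.29 | 10.0 | 3.6 |

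Because baseline CDQ24 is collected, the adjusted column is the fair comparator.

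**The case against.** **The schedule itself cannot be seen.** The article refers the reader to Fig. 2 for the examinations at each visit, and that figure was not available for this review. It may list CDQ24 at Motor visit 2. The Motor visit 2 sentence presents the assessments as done for a third time, which reads like a repeat of the same battery, and CGI appears nowhere else. A slip of CGI for CDQ24 is plausible. This stands, and it limits the point to the text. It does not remove it: if the figure does list CDQ24, text and figure disagree and need aligning.

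**Quality of life can still be compared.** This also stands. A reader might infer that the planned quality-of-life comparison and its correlation with motor data are impossible altogether, or that the programs can never be compared on CDQ24. The documents do not support either. The analysis sentence speaks of quality of life without naming an instrument, SF-36 is taken at both motor visits, and a randomized between-patient CDQ24 comparison remains at Motor visit 1.

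**The loss is easily overstated.** A 4- to 10-fold variance penalty arises only if baseline CDQ24 is ignored. With adjustment it is 3.0 to 3.6. The split, the correlations and the power target are assumptions, the plan sets no power for any secondary endpoint, and the trial may stop with fewer than 40 patients.

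**The trial is exploratory.** Its stated aim is to estimate a success rate and explore treatment failures in preparation for a confirmatory trial, and quality of life is examined for clinical plausibility. This lowers the severity. It does not reconcile the passages.

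**Conclusion.** The point holds for the text, with moderate severity. A named secondary endpoint, to be analysed by paired methods and checked for carry-over, has no second-period measurement in the visit description. Followed literally, that gives 0 of 40 CDQ24 pairs and leaves a between-patient comparison at Motor visit 1 whose detectable difference, with baseline adjustment, is about 1.7 to 1.9 times that of 40 pairs (0.79/0.45 and 0.55/0.29, being √3.0 and √3.6). This size rests on the assumptions listed above, including the same ρ for both correlations.

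The primary endpoint, n = 40, the cut-offs and the paired SF-36 analysis are untouched, so this is not a defect that undermines the trial's main result. Nor do the documents show that CDQ24 was dropped on purpose. What they show is an inconsistency between the visit text and the endpoint and analysis sections.

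**What to change.** - List CDQ24 at Motor visit 2 alongside SF-36, and make the visit text, Fig. 2 and the case report form agree.
- State whether CGI at Motor visit 2 is a slip for CDQ24 or an additional measure and, if additional, what it is for. CGI is not a named endpoint, so nothing in the article requires it at both motor visits.
- If CDQ24 is deliberately not collected at Motor visit 2, remove it as an endpoint for the within-patient comparison of programs and describe the Motor visit 1 comparison, adjusted for baseline, as what it is.

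The cost of the first option is one extra questionnaire per patient at a visit that already takes place, plus a correction to the visit table and case report form. Sample size, visit timing and the primary analysis do not change.
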